### Intervention

2.5

#### Application development

2.5.1

The development process for the ReMindCare app can be divided into different phases, including review of the literature, a survey study, a design phase, a pilot study phase and a final version phase.

We first conducted a systematic review of previous publications on apps for psychosis (Bonet et al., 2017). Although the results of this review suggested that apps are feasible and well accepted by patients with psychosis, and apps can capture symptoms with good correlation to traditional metrics, a lack of clinical integration was notable across nearly all studies. Thus, to better understand how to design an app optimized for clinical integration, we next conducted a survey study of patient interests and preferences. We designed a survey based on previous publications (Borzekowski et al., 2009; Gay, Torous, Joseph, Pandya, & Duckworth, 2016; INE, 2016; Miller, Stewart, Schrimsher, Peeples, & Buckley, 2015; NAMI, 2014; Robotham, Satkunanathan, Doughty, & Wykes, 2016; Trefflich, Kalckreuth, Mergl, & Rummel‐Kluge, 2015) and administered it to a sample of 113 patients with psychosis. We aimed to evaluate the actual feasibility of e‐health interventions in a potential sample of patients with psychosis in our target population and to evaluate the interest of these patients in e‐health interventions (Bonet et al., 2018). The results highlighted that apps must offer improved communication with clinicians.

Next, we codesigned an e‐health app called ReMindCare with a team of clinicians, patients and developers. Our main objective of this process was to ensure the usability of the app. In this regard, both the patients and prior work in this space led us to focus on displaying information in the app graphically to easily allow a quick overview of the results and analysis of relevant information. We used a set of information technologies that simplified the development and communication between different parts of the platform. This included utilizing free and open source software tools such as the MongoDB database (MongoDB, GNU AGPL v3.0) to ensure flexibility and scalability, a Node.js server (Node.js, MIT Licence) to power the app, Docker containers (Docker, Apache Licence 2.0.) to protect privacy and frameworks such as Meteor and Bootstrap to build responsive user interfaces. This development of the app was conducted in a test environment outside the hospital network. Early efforts in this phase were focused on proper functioning of the database, the website and the mobile application.

With a functional first version of the ReMindCare app, we next focused on the challenges related to integration of the app into the hospital system. First, we had to study the current digital infrastructure of the hospital and adapt the platform to achieve its integration into the system while ensuring the performance of the app remained as designed, and patient data privacy was maintained. User authentication around the identification of both physicians and patients was a barrier that we faced. This identification was carried out through the Lightweight Directory Access Protocol (LDAP), which allows access to an organized and distributed directory service for an information search. The identification of patients and the report uploading was realized using Health Level Seven (HL7), which is an international set of standards to facilitate the electronic exchange of clinical information. This development process and installation of the app took approximately 2 years, with the most time spent on the clinical integration of the app into the hospital electronic system.

Although the process of integration was underway, we conducted a pilot study to test the validity and usability of the platform. This pilot trial involved four patients with psychosis for a period of 3 months, during which no negative effects associated with app use were found. The rates of compliance to surveys within the app were between 90% and 97%. Based on user feedback, we conducted further modifications to ensure the accurate functioning of the app in regards clinicians access to the app website, privacy of data registration and technical and electronic adjustments to achieve the automatic synchronization of ReMindCare with Android updates to ensure the appropriate performance of the app among different Android versions and smartphones.

#### 
ReMindCare app

2.5.2

ReMindCare is a free and user‐friendly app that conducts daily evaluations of the health status of patients with psychosis by offering quick questionnaires. Two types of questionnaires are presented (Figure 1):
*Daily questionnaires*: Three daily questions that assess levels of anxiety, sadness and irritability.
*Weekly questionnaires*: Eighteen weekly questions aimed to assess adherence to medication (1), the presence of side‐effects to anti‐psychotic medication intake (5), the attitude towards medication intake (3) and the presence of prodromal psychosis symptoms (9).

**FIGURE 1 eip12960-fig-0001:**
[figure not shown]
Screen shot of the ReMindCare dashboard (App for patients). Example of daily evaluation questions

To use this clinical tool, clinicians enrol their patients via a private portal. Once the patients are registered into the portal, they can download the app, which is available on “Google Play,” log into the app and begin to use it. Patients are instructed on how to download and log into the app, and they are informed regarding how their app data are used.

The information gathered by the app is accessible to clinicians on the portal, and it is exclusively used to orient clinicians for upcoming visits with patients, to help both patients and clinicians have a shared vision of the status of the patient and to discuss and establish together the therapeutic approaches. In addition, as displayed in Figures 2 and 3, on this portal, clinicians can not only visualize the information but also generate a PDF report that summarizes this information. These reports can be uploaded to the electronic medical record (EMR) of the patient because we enabled a function in the electronic hospital system that allows the inclusion of the ReMindCare app reports as another type of clinical report (eg, similar to results from a blood pressure test or glucose test). Moreover, if patients do not respond to notifications or abrupt variation in their answers occurs, the system automatically generates “alarms or warnings.” These alarms notify the clinician by e‐mail and are also displayed in the profile of the patient on the website. Moreover, patients are able to contact their clinician using an “Urgent Consultation” tab displayed on the app if they detect a significant worsening in their health status. By clicking this button, clinicians receive a notification e‐mail and have to contact the patient within a maximum period of 48 hours. Further information about the use of the app and the webpage is available in the user manual included in Appendix A.

**FIGURE 2 eip12960-fig-0002:**
[figure not shown]
Screen shot of the ReMindCare dashboard (Website for clinicians). List of questions presented to patients

**FIGURE 3 eip12960-fig-0003:**
[figure not shown]
Screen shot of the ReMindCare Dashboard (for clinicians). Example of daily evaluation graphics

### Data collection and measures

2.6

An overview of all included measures and assessment points is included in Table 1.

**TABLE 1 eip12960-tbl-0001:** Study measures and assessment times

Timepoint	ReMindCare intervention					
	Baseline	Intervention			Follow‐up	
	*t* _0_	*t* _1_	*t* _2_	*t* _3_	*t* _4_	*t* _5‐8_
Enrolment						
Eligibility screen	X					
Informed consent	X					
Assessments						
Baseline assessment						
Clinical Global Impression Scale (CGI) (Busner & Targum, 2007)	X				X	X
Global Assessment of Functioning (GAF) (Endicott, Spitzer, Fleiss, & Cohen, 1976)	X				X	X
Positive and Negative Syndrome Scale (PANSS) (Peralta & Cuesta, 1994)	X				X	X
Premorbid Adjustment Scale (PAS) (Cannon‐Spoor, Potkin, & Wyatt, 1982)	X				X	X
Drug Attitude Inventory (DAI‐10) (Hogan, Awad, & Eastwood, 1983)	X				X	X
Beck Cognitive Insight Scale (BCIS) (Beck, Baruch, Balter, Steer, & Warman, 2004)	X				X	X
Sociodemographic information (Age, sex, ethnicity, marital status, level of education, living situation and employment status)	X					
Clinical information (Diagnose, years of illness, pharmacological treatment, suicidal attempts, history of illness)	X		X		X	X
Outcome measures						
Simplified Medication Adherence Questionnaire (SMAQ) (Morisky, Green, & Levine, 1986)	X		X		X	X
Number of relapses	X		X		X	X
Number of visits to urgent care units at the hospital	X		X		X	X
Number of hospital admissions	X		X		X	X
ReMindCare measures						
Answers to questionnaires		X	X		X	X
Quantity of “urgent consultation” requests		X	X		X	X
Quantity of alarms generated		X	X		X	X
Satisfaction Questionnaire^†^				X		X

Note: *t*
_1_ = introduction of the ReMindCare app into clinical practice; *t*
_2_ = first‐year preliminary data assessment; *t*
_3_ = focus group, first year; *t*
_4_ = second‐year follow‐up; *t*
_5‐8_ = fifth‐year follow‐up; Satisfaction questionnaire^†^ = App feedback questionnaire made for the purpose of this research.

Baseline surveys, including clinical and sociodemographic information and clinical standardized questionnaires, were administered before the enrolment of the patient in the study. As shown in Table 1, data regarding the main outcomes, such as adherence to medication, number of relapses, number of visits to the hospital urgent care units and number of hospital admissions, will be collected and analysed at the end of the first, second and fifth years of the intervention. Moreover, information generated for patients through the use of the app will also be analysed at the same timepoints. Finally, to analyse the feedback of patients regarding the use of the app, we plan to conduct focus groups at the end of the first year of the intervention, and we have also designed a “satisfaction questionnaire” (SQ) that patients will complete at the end of the first year of the intervention or before discontinuing the use of the app (if discontinuation occurs before the first year of app usage). This SQ was made for the purpose of this research study and is based on previous satisfaction and usability questionnaires, such as the user version of the Mobile Application Rating Scale (uMARS) (Stoyanov, Hides, Kavanagh, & Wilson, 2016), the System Usability Scale (SUS) (Brooke, 1996), EnLight: a tool for mobile and web‐based eHealth interventions (Baumel, Faber, Mathur, Kane, & Muench, 2017) and the App Quality Evaluation (AQEL) (DiFilippo, Huang, & Chapman‐Novakofski, 2017). This questionnaire is displayed in Appendix B.

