#### Recruitment and enrolment

2.4.1

Every outpatient from the FEPP who meets the criteria for inclusion is considered a potential user of the ReMindCare app. Once patients enrol in the study, they are able to use the app for a maximum period of 5 years, which is the time when they would be discharged from the FEPP.

All patients interested in using the app must sign an informed consent form and must complete some baseline assessments before their inclusion in the study.

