#### Discontinuation and withdrawal

2.4.3

A patient's participation in the study will be discontinued if:The patient provides an explicit notification of not wishing to continue using the app.Lack of use the app for a period longer than 2 months after having been contacted by the research group over that period of inactivity.Discharged from the FEPP or if their consent is revoked.Given the naturalistic nature of this study, in case of discontinuation or withdrawal, patients will continue with the usual psychiatric treatment at the hospital.

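### The text and Table 1 disagree on a fifth-year satisfaction questionnaire, and patients who stop after year 1 get no exit rating, so any fifth-year result describes continuing users only

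*Protocol article*

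**What the plan says.** Section 2.6 (Data collection and measures) describes a purpose-made satisfaction questionnaire that "patients will complete at the end of the first year of the intervention or before discontinuing the use of the app". The exit version carries a restriction, since it is given "before discontinuing the use of the app (if discontinuation occurs before the first year of app usage". The text names no later administration.

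Table 1, in the same section, has a row for the "Satisfaction Questionnaire" with two marks. One is at t3, which the note defines as "focus group, first year". The other is at t5-8, which the note defines as the fifth-year follow-up. The cell for year 2 (t4) is empty.

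Section 2.4.1 says of enrolled patients that "they are able to use the app for a maximum period of 5 years". Section 2.4.3 ends participation on the patient's request, on discharge from the programme, on revoked consent, or for inactivity: "Lack of use the app for a period longer than 2 months after having been contacted by the research group". None of these routes is tied to a particular year.

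Satisfaction and perceived usability form the third study aim (section 2.1). Section 4.1 also names the questionnaire, with focus groups, as the means of assessing patient-clinician communication.

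**The concern.** Two published schedules for one instrument differ on whether it is repeated at year 5. Read together, they also leave a gap. The exit rating is available to patients who stop in the first year and not to those who stop in the following four. Someone who stops in that later period is no longer participating when the fifth-year questionnaire falls due.

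At stake is how a fifth-year result under aim 3 would be read. Section 2.7 plans further analysis at the end of years 2 and 5. A fifth-year satisfaction figure reported without qualification would look like the view of the app's users, when it is the view of those who kept using it. The opinions formed by people at the point of giving up the app, which bear directly on its acceptability over the longer term, would not have been collected.

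**Working it through.** **Step 1: the schedules side by side.**

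| Time | Text of 2.6 | Table 1 |
|---|---|---|
| Stops before year 1 | Questionnaire at exit | No exit column |
| Year 1 | Questionnaire | Marked (t3) |
| Stops between years 1 and 5 | None | None |
| Year 2 | None | Empty (t4) |
| Year 5 | Not mentioned | Marked (t5-8) |

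The text and the table differ on year 5. Neither provides a rating for a patient who stops between years 1 and 5.

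**Step 2: what each group is scheduled to give.**

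- Stops before year 1: one rating, at exit.
- Stops between years 1 and 5: one rating, at year 1.
- Still using the app at year 5: ratings at year 1 and, if Table 1 holds, at year 5.

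Every patient is therefore scheduled for at least one rating. What is missing is the later leavers' view when they leave.

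**Step 3: how many patients this could involve (illustration only).** The document gives no figure to reproduce. It reports 57 patients enrolled at the time of writing (section 3), with enrolment continuing, and an expected retention above 70% with no time horizon (section 4.1). Assume a constant annual retention r. Then:

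- present at year 1 = 57 × r
- present at year 5 = 57 × r^5
- leave in between, as a share of those present at year 1: f = 1 − r^4

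| Assumed r | Year 1 | Year 5 | Leave in between | f |
|---|---|---|---|---|
| 0.95 | 54.1 | 44.1 | 10.0 | 0.185 |
| 0.931 (70% kept over five years, 0.7^(1/5)) | 53.1 | 39.9 | 13.2 | 0.248 |
| 0.90 | 51.3 | 33.7 | 17.6 | 0.344 |
| 0.80 | 45.6 | 18.7 | 26.9 | 0.590 |
| 0.70 | 39.9 | 9.6 | 30.3 | 0.760 |

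**Step 4: effect on a fifth-year mean.** Let D be the mean rating of stayers minus that of later leavers. The stayers-only mean then exceeds the mean for all who reached year 1 by f × D. With 70% kept over five years this is about 0.25 × D, and with 70% kept each year about 0.76 × D. The document gives neither the size nor the sign of D, so this shows the form of the effect and not its amount.

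**Step 5: what the scheduled data can already show.** Stayers and later leavers both have a year-1 rating. The difference between their year-1 means estimates the selection that already existed at year 1. It cannot show a change of view between year 1 and leaving.

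**The case against.** The strongest reply is that the plan already asks everyone once. The early-exit rule catches those who would otherwise give no rating, and later leavers have answered at year 1. Section 2.7 places the preliminary satisfaction results at the end of the first year, and that analysis is untouched. All of this stands. It confines the point to a fifth-year result.

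It can also be said that the conflict is soft. The text does not say the questionnaire is given only once, and Table 1 is presented as the overview of all measures and time points. The text may simply be describing first-year feedback. That is a possible reading, but a reader has to guess it, and the t5-8 label (several time points explained as one follow-up) does not help. It leaves the exit gap in place in any case.

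Three stronger readings are tempting, and the document does not support them.

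- A reader might infer that a year-1 to year-5 comparison would show satisfaction rising even if no one's view changed. That would happen only if all year-1 responders were compared with year-5 stayers and D were positive. No such comparison is planned. A comparison within the same patients would show no change if no view had changed.
- A reader might infer that the fifth-year result must be too favourable. That needs leavers to be less satisfied. Discharge from the programme is one of the discontinuation routes. Patients enter with any illness duration under 5 years, so some may be discharged before five years of app use for reasons unrelated to the app.
- A reader might take the counts in step 3 as forecasts. They rest on an assumed retention horizon and an interim enrolment count.

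**Conclusion.** The point holds in a limited form. Section 2.6 and Table 1 do not agree on a fifth-year satisfaction questionnaire. As written, patients who stop between years 1 and 5 give no rating on leaving, so any fifth-year result describes continuing users only and may not represent all users. This last step relies on section 2.4.3 ending study participation at discontinuation, with no later questionnaire provided for those who have stopped.

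The direction is probably favourable to the app if leavers are less satisfied, which is an assumption. The size cannot be computed from the document. The year-1 satisfaction result and the main outcomes listed in section 2.6 (medication adherence, relapses, urgent care visits and admissions) are not affected. This is a small, worthwhile improvement and not a flaw that threatens the study.

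**What to change.** 1. Make the text of section 2.6 and Table 1 agree on whether the questionnaire is given at year 5.
2. Remove the first-year limit on the exit version, so that the existing questionnaire is offered at any discontinuation, whenever it occurs. For inactive patients, use the contact that section 2.4.3 already describes.
3. Label any fifth-year result as applying to continuing users.
4. Report exit ratings separately, by reason for leaving and with the response rate among leavers. Do not pool them with year-5 ratings as fifth-year satisfaction, because that mixes time points.
5. Make any year-1 to year-5 comparison within the same patients.
6. Compare the year-1 ratings of later leavers and stayers, to show how selected the continuing users are.

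The cost is a wording change, one existing questionnaire at exit, and a few extra lines in the report. The downside is non-response: some leavers, including those who revoke consent, will not reply, so the exit ratings will themselves be incomplete.

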### Planned data analysis

2.7

Descriptive analyses of sociodemographic and clinical variables will be conducted. A multivariate data analysis will be carried out to explore relationships between sociodemographic and clinical variables and adherence to treatment and ReMindCare measures. An ANOVA model of repeated measures will be used for the main research outcomes. All analyses will be conducted with an alpha set at *P* < 0.05.

These preliminary quantitative data analyses and the preliminary results regarding patient compliance, retention rate and perceived satisfaction with the use of the ReMindCare app are expected by the end of the first year of using the app (March 2020). At that time, qualitative analyses of data are also planned.

Subsequent analysis of the data will be conducted at the end of the second and fifth years of use of the app.

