### Study setting

2.3

The ReMindCare app was systematically integrated into the daily FEPP workflow at the Public Clinical Hospital of Valencia (Spain), where it is currently being used. This FEPP is a free care service that aims to enhance the quality of the early care of outpatients with a first episode of psychosis, from the early phases of the illness through the first five critical years of treatment (Arango et al., 2017).

Given the pragmatic and naturalistic nature of this study, no remuneration or compensation is offered to patients participating in the programme or using the app. Rather, the app is offered as an additional and free service to the patients in treatment at study sites.

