#### Eligibility criteria

2.4.2

To be considered for this study, patients must be accepted into the FEPP at the Clinical Hospital of Valencia. Criteria for inclusion in the FEPP are:Diagnosis of psychotic disorder following DSM‐5 (APA, 2013) criteria, interview conducted by a licensed clinician.Less than 5 years of illness duration.Residence associated with the hospital area of correspondence (Area 5 of Valencia).Age between 17 and 65 years oldOwnership of a smartphone with an internet connection that allows the proper installation and functioning of the app.

Exclusion criteria include the following:Inability to use and master a mobile device and the Internet.Refusal to sign an informed consent form.Spanish/English language fluency limiting ability to partake in clinical conversations or to understand the app questionnaires.

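### For patients enrolled before their first remission, the baseline relapse count is fixed by eligibility, so it should not be a level of the repeated-measures ANOVA of relapses

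*Protocol article*

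**What the plan says.** Table 1 (section 2.6) places "Number of relapses" under outcome measures and marks it at t0, t2, t4 and t5-8. The text below the table speaks of "data regarding the main outcomes, such as adherence to medication, number of relapses" and other items, to be analysed after years 1, 2 and 5. Section 2.7 then fixes the model: "An ANOVA model of repeated measures will be used for the main research outcomes".

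Section 2.3 describes a service for "outpatients with a first episode of psychosis, from the early phases of the illness through the first five critical years of treatment". Among the entry criteria in section 2.4.2 are "Diagnosis of psychotic disorder following DSM"-5 and "Less than 5 years of illness duration". No lower limit on duration and no remission requirement appears. Section 2.4.1 opens enrolment widely: "Every outpatient from the FEPP who meets the criteria for inclusion is considered a potential user of the ReMindCare app".

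Section 4.2 adds that the main outcomes will be compared between app users and age-matched controls, and concedes that the groups may differ. The article gives no relapse rate, no share of patients enrolled during a first episode and no sample size. Section 3 reports 57 patients enrolled so far.

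**The concern.** On the ordinary meaning of the word, a relapse needs an earlier episode that has remitted. A patient who enrols while still in the first episode has had no opportunity to relapse. The t0 count for that patient reflects stage of illness at entry and says nothing about a relapse rate under usual care. The year-1 count does include time after remission, so it can rise but not fall. A second group is also mis-scored: a patient who never remits during app use cannot relapse, and would carry the same zero as a patient who remitted and stayed well.

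A common look-back window, which the full protocol may well specify, does not help, because twelve months before entry still gives a fixed value for anyone in a first episode. If the qualifying episode is itself counted, the fixed value becomes 1 and the forced change runs the other way.

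Relapse is a main outcome, and early detection of relapses is part of Aim 1. The within-patient time effect could show worsening or improvement that comes only from who was enrolled.

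**Working it through.** **Which levels the ANOVA has.** Table 1 marks relapses at t0 and t2 but not at t1 or t3. At the first planned analysis, at the end of year 1, t0 and t2 are the only values available. A repeated-measures ANOVA at that point must use t0 as a level, and with two levels in one group it equals a paired t-test.

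**Inputs.**
- From the article: n = 57 (section 3); alpha 0.05 (section 2.7).
- Assumed, because the article gives none of these: a two-sided test; share f of patients entering in the first episode; entry spread evenly over 0 to 0.5 years after onset; remission at 0.5 years; relapse rate r = 0.3 per year once remitted; Poisson counts; a common 12-month window; no app effect.

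**Expected means.** First-episode entrants wait on average 0.25 years for remission, so they are at risk for 0.75 of year 1 and have 0.3 × 0.75 = 0.225 expected relapses.
- Baseline, qualifying episode not counted: (1 − f) × 0.3
- Baseline, qualifying episode counted: (1 − f) × 0.3 + f × 1
- Year 1: (1 − f) × 0.3 + f × 0.225

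For f = 0.4 these are 0.6 × 0.3 = 0.18; 0.18 + 0.4 = 0.58; and 0.18 + 0.09 = 0.27.

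**False significance by simulation** (paired test; percentages vary by about a point between runs):

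| Share f | Baseline, not counted | Baseline, counted | Year 1 | Significant, not counted | Significant, counted |
|---|---|---|---|---|---|
| 10% | 0.27 | 0.37 | 0.2925 | about 6% | about 12% |
| 20% | 0.24 | 0.44 | 0.285 | about 7% | about 33% |
| 40% | 0.18 | 0.58 | 0.27 | about 18% | about 82% |
| 60% | 0.12 | 0.72 | 0.255 | about 37% | about 99% |

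With no first-episode entrants the rate is 5%, as it should be. When the episode is not counted, almost all significant results are rises from the 20% share up. When it is counted, they are almost all falls. Rates of 0.2 to 0.4 per year give the same pattern.

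**Never-remitters.** If 30% of first-episode entrants never remit at f = 0.4, the year-1 mean is 0.18 + 0.4 × 0.7 × 0.225 = 0.243 instead of 0.27, although nothing has improved.

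**Which share is plausible.** If illness duration at entry were uniform over 0 to 5 years, 0.5/5 = 10% would enter in the first six months. Larger shares need recruitment nearer onset, which the article neither states nor excludes.

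**Is the baseline zero for everyone?** With duration uniform over 0 to 5 years and relapse rate r throughout, the chance of at least one earlier relapse is 1 − (1 − e^(−5r))/(5r). At r = 0.1 this is 21%, and at r = 0.4 it is 57%, or about 12 to 32 of 57 patients. Their counts can fall.

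**The case against.** A reader might infer from the programme's name that every participant is in a first episode, so that the whole baseline is zero and relapses can only stay level or rise. The article does not support this. The service covers patients "from the early phases of the illness through the first five critical years of treatment", and entry allows almost five years of illness with earlier relapses. The direction of the bias also depends on whether the qualifying episode is counted, which the article does not state.

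Three further objections have weight.
- **Size.** At the 10% share that evenly spread durations imply, false significance is close to nominal unless the qualifying episode is counted. This stands. The large figures need larger shares.
- **Other planned comparisons.** Section 4.1 ties explicit baseline-to-year-1 contrasts to medication adherence and insight, and frames relapse mainly through app engagement and use of the urgent-consultation function. Section 4.2 adds controls. Even so, section 2.7 assigns all main outcomes to the one model. The controls would cancel the bias only if they held the same share of first-episode patients, and age matching does not secure that.
- **Unseen definitions.** A condensed article may leave the relapse definition and look-back window to the full protocol, and their absence is no fault here. The fixed baseline remains under any window, and the definition decides only whether it is 0 or 1.

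**Conclusion.** The concern holds for patients enrolled before their first remission. Eligibility admits them, their t0 relapse count is set by that eligibility, and the year-1 repeated-measures ANOVA has to use it. It does not hold as a statement about the whole cohort.

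The size is uncertain. Under the assumptions above it runs from negligible (about 6% false significance at a 10% share) to serious (about 37% at 60%), and it is larger and in the opposite direction if the qualifying episode is counted. The share, relapse rate and time to remission are all assumed. That the t0 count is not comparable for these patients does not depend on those values. The change is worth making because relapse is a main outcome and the change is cheap.

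**What to change.** In section 2.7, do not use the t0 relapse count as a level of the repeated-measures ANOVA. Keep it as a descriptive history variable or a covariate.

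Analyse post-baseline relapses as a rate per person-year of follow-up, for example by Poisson or negative binomial regression with follow-up time as an offset. Compare users with the planned age-matched controls from a matched index date, adjusting for illness duration and, where recorded, remission status at index. State that the qualifying episode is not counted as a relapse, and report patients who never remit separately.

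Use time at risk from first remission only as a sensitivity analysis. It needs a remission criterion that the article does not give. Table 1 does not mark the PANSS or CGI at t2, so dating remission in year 1 would rest on chart review.

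The main analysis needs revised wording and no new patients or visits. An index date, illness duration and, where available, remission status are needed for the controls as well. The downside is the loss of a within-patient baseline-to-year-1 contrast for relapse.
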